### Randomization

After baseline evaluation, eligible patients will be randomly assigned to either the AG or SA group in a 1:1 ratio using computer-generated random numbers. Before randomization, all participants will be informed of their potential allocation to either group. The allocation sequence will be concealed using sealed, opaque, sequentially numbered envelopes, which will only be opened upon enrollment of eligible participants. Independent statisticians, uninvolved in participant recruitment, evaluation, and intervention, will be responsible for the sequence generation and allocation process throughout the study. The detailed standard operating procedure for envelope management is provided in S4 File.

### Blinding

This study will employ the single-blinded method. Patients will be treated separately to ensure blind evaluation. A third-party assessors who do not know group assignments will assess outcomes. Due to the unique nature of acupuncture procedures (including sensations and depth), it will not be possible to blind the acupuncturists. However, all other research personnel, including research fellows, outcome assessors, and statisticians, will be blinded to randomization results,study procedure and any treatment interventions for the entire study duration. To maintain consistency, each patient will be assessed by the same evaluator. When participants complete all 24 acupuncture sessions, they will be asked whether they received real or sham acupuncture to assess blinding effects. Efficacy evaluators and statisticians will be separated and blinded. Additionally, at the 12-week and 60-week time points, a simplified blinding assessment questionnaire will be administered to all outcome assessors. The questionnaire will inquire about their guess regarding the group assignment (AG, SA, or unclear) of the evaluated participant. The responses will be analyzed using the James’ blinding index to objectively evaluate the maintenance of blinding.

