### Outcomes

#### Primary outcome measures.

Cognitive function will be measured using the ADAS-Cog scale [35]. The primary outcomes will be the changes in the ADAS-Cog score from baseline to week 12 and from baseline to week 60. The ADAS-Cog, comprised of 12 tasks, evaluates various aspects of cognition, including memory, language, praxis (ability to perform actions), orientation, and attention. It is a widely used instrument in dementia research, with lower scores indicating less cognitive impairment.

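### James' index, the only index named for assessor blinding, cannot fall below the share of 'unclear' answers, so it could look favourable even if every guess made is right; a per-arm index should stand beside it

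*Protocol article*

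**What the plan says.** The Blinding section of the protocol article has outcomes rated by independent assessors: "A third-party assessors who do not know group assignments will assess outcomes". The practitioners know the allocation, since "it will not be possible to blind the acupuncturists".

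Assessor blinding is then checked: "at the 12-week and 60-week time points, a simplified blinding assessment questionnaire will be administered to all outcome assessors". There are three possible answers: "The questionnaire will inquire about their guess regarding the group assignment (AG, SA, or unclear) of the evaluated participant". One analysis is named: "The responses will be analyzed using the James’ blinding index to objectively evaluate the maintenance of blinding".

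Neither the Blinding section nor the Statistical analysis section gives a second index, a per-arm analysis, a table of answers by arm, or a value at which blinding would be called maintained. The two questionnaire times are also the two primary time points: "The primary outcomes will be the changes in the ADAS-Cog score from baseline to week 12 and from baseline to week 60".

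**The concern.** James' index measures overall blinding and gives full credit to 'unclear'. A third-party rater who does not see treatment may well give that answer often. The index then rises because of the 'unclear' answers, however accurate the remaining guesses are. Because it pools the arms, it also cannot show that one arm was recognised and the other was not.

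Partial disclosure is plausible here. The practitioners are unblinded, and Tables 2 and 4 show that the needle sites differ visibly. Active treatment uses the head, ankle and inner calf; sham uses the arms and the outer side of the shin. A participant's chance remark could reveal the arm for that participant while other answers stay 'unclear'.

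What is at stake is how far the trial can support a statement that its raters were blind when scoring ADAS-Cog at both primary time points. The planned difference is 2 points with SD 3.5 (Sample size section), so readers will want evidence that rating was not influenced.

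**Working it through.** **Inputs.** From the Sample size section: 83 enrolled per arm; 132 evaluable in total, or 66 per arm. From the Blinding section: answers AG, SA or unclear. Assumed, because the document gives neither: the 'unclear' share and the proportion of guesses that are right.

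**The plan's own figures.** No index value is stated, so only the sample size can be reproduced. A two-sample t calculation with difference 3.5 − 1.5 = 2.0, SD 3.5, two-sided α 0.05 and power 0.90 gives 65.3, so 66 per arm and 132 in total. Then 132 / 0.80 = 165, made even at 166, or 83 per arm.

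**James' index.** With P the share of 'unclear' answers,

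James = [1 + P + (1 − P) × K] / 2, where K = (D_obs − D_exp) / D_exp.

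D_obs is the weighted disagreement among those who guess (right guess 0, wrong guess 0.5). D_exp is its value expected by chance. All 'unclear' gives 1; random guessing with no 'unclear' gives 0.5.

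**Lower bound.** D_obs cannot be negative, so K ≥ −1 and James ≥ [1 + P − (1 − P)] / 2 = P. Equality holds when every guess is right. Hence P > 0.5 forces James > 0.5.

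**Bang's index**, per arm: (right − wrong) / all answers in that arm. Zero means no excess of right guesses.

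**Every guess right, 83 per arm** (James with resampling 95% interval):

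| 'Unclear' per arm | James | Bang, each arm |
|---|---|---|
| 17 (20%) | 0.20 (0.14 to 0.27) | 0.80 |
| 33 (40%) | 0.40 (0.33 to 0.48) | 0.60 |
| 42 (about 50%) | 0.51 (0.43 to 0.58) | 0.49 |
| 50 (60%) | 0.60 (0.53 to 0.68) | 0.40 |
| 58 (70%) | 0.70 (0.63 to 0.77) | 0.30 |
| 66 (80%) | 0.80 (0.74 to 0.86) | 0.20 |

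At 60%, Bang = 33/83 = 0.398. Its variance is (0.398 − 0.398²)/83 = 0.00289, SE 0.054, so the 95% CI is 0.29 to 0.50 in each arm. With 66 per arm the James value is 0.61 (0.52 to 0.69).

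The upper limit for James reaches 0.5 at about 42% 'unclear' (35/83 = 0.42, interval 0.35 to 0.50).

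**Guesses mostly right.** Take 50 'unclear', 27 right and 6 wrong per arm.
- James: D_obs = 0.5 × 6/33 = 0.091, D_exp = 0.25, K = −0.636. James = [1 + 0.602 + 0.398 × (−0.636)] / 2 = 0.67.
- Bang: (27 − 6)/83 = 0.25 per arm, 95% CI 0.13 to 0.38.

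**Only one arm recognised.** Let every AG guess be right and SA guesses be random, with equal 'unclear' shares.
- D_obs = 0.5 × 0.25 = 0.125, D_exp = 0.25, K = −0.5, so James = 0.25 + 0.75 × P. This passes 0.5 once P exceeds one third.
- At P = 0.40, James = 0.55, while Bang is 0.60 in AG and 0 in SA.

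**The case against.** Several objections have force.

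- **No decision rule is stated.** The value 0.5 comes from the scale of the index, not from a rule in the protocol. A James value of 0.60 can be read literally as 60% of responses showing no knowledge of the arm, which is accurate in the illustration. This stands: a reader might infer that the trial will declare blinding maintained, and the document does not say so. A stricter cut-off would move the problem to a higher 'unclear' share but would not remove the dependence on it.
- **James' index is a standard choice, and the article does not say it will be used exclusively.** Also right. The full protocol or analysis plan may add a per-arm measure. But the article fixes one named index for this purpose, so the limits of that index are a fair subject. Nothing here requires dropping or demoting it.
- **The illustration is an adverse case.** With 40% or less 'unclear' and every guess right, the upper limit for James stays below 0.5 and the index does signal unblinding. The favourable appearance arises in only part of the range, and no passage says which part applies. Nor does any passage support a claim that assessors have a motive to answer 'unclear'.
- **Safeguards exist.** Raters are third parties, participants are treated separately, and practitioners are told not to discuss treatment. These lower the risk of disclosure without removing it.
- **Right guesses need not mean leakage.** If acupuncture works, improvement may be visible by weeks 12 and 60. Bang's index cannot separate the two causes either.

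A reader might also count it as a fault that "each patient will be assessed by the same evaluator". The protocol gives consistency as the reason, and the property of James' index does not depend on that choice.

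**Conclusion.** The point holds in a limited form. The lower bound is exact: James' index is at least the 'unclear' share, and it exceeds 0.5 whenever most responses are 'unclear', however accurate the guesses are. At 60% 'unclear' with all guesses right it is about 0.60, against about 0.40 for Bang's index in each arm. At 27 of 33 guesses right per arm the values are 0.67 and 0.25.

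These figures rest on assumed 'unclear' and accuracy rates, on 83 responses per arm, and on independent guesses. With about 66 per arm, and with several participants per rater, the intervals would be wider than shown.

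The documents do not support the stronger conclusion that unblinded rating will go undetected or that the primary result is biased. The primary estimate and the sample size do not depend on the index. What is affected is how informative the planned blinding check will be at the two primary time points. This is a cheap improvement.

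**What to change.** Keep James' index and add three things to the assessor blinding analysis at weeks 12 and 60:

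1. Bang's index with a 95% confidence interval, separately for AG and SA, allowing for several participants rated by the same assessor where the data permit.
2. The table of answers (AG, SA, unclear) by actual arm.
3. An instruction that each guess is recorded only after that visit's scales are final.

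State in the plan that a positive index will be interpreted with caution, since it may reflect visible response to treatment as well as disclosure of the arm.

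The cost is one extra table and a short procedural instruction. The same questionnaire answers serve, with no additional visits or participants. The one drawback for the trial is that the reported blinding result may look less favourable.

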### Sample size

The Alzheimer’s Disease Assessment Scale-Cognitive (ADAS-Cog) score will serve as the primary index to evaluate cognitive function improvement in patients with MCI. The sample size calculation for this trial was based on our previous study [30] and pilot study, we anticipate an average effect of 3.5 in the acupuncture group and 1.5 in the control group, with a standard deviation of 3.5 between the groups. Using PASS software, we calculated a required sample size of 132 subjects (α = 0.05, 1 − β = 0.90, two-sided). To account for a potential 20% loss to follow-up, we plan to enroll 83 patients in each group, for a total of 166 aMCI patients in the study.

### Interventions

Both groups will receive the same number of acupuncture sessions, with identical treatment frequency and duration. To ensure standardization, all interventions will be performed by licensed Traditional Chinese Medicine acupuncturists with more than 6 years of experience, and these practitioners will administer both real and sham acupuncture.

#### Acupuncture group.

Acupuncture treatment will adhere to the Standards for Reporting Interventions in Controlled Trials (STRICTA) [31] (**Table 1**). The following acupoints will be used: bilateral Taixi (KI 3), bilateral Dazhong(KI 4), bilateral Sanyinjiao (SP 6), Shenting (GV 24), and Baihui (GV 20) (**Table 2**). Licensed acupuncturists will follow TCM standards for acupoint location and manipulation. After skin disinfection, acupuncturists will insert single-use sterile needles (Hwato, Suzhou, China; 0.25 × 25 mm) into the acupoints. A uniform reinforcing-reducing method will be employed, involving twisting, thrusting, and rotation to elicit the *deqi* sensation within the patient’s tolerance. Needles will be manually manipulated every 10 minutes to maintain the *deqi* sensation, with a twisting angle of 90–180 degrees, a frequency of 60–90 times/minute, and a lifting and inserting amplitude of 3–5 mm. Treatment sessions will last 30 minutes and continue for 12 weeks, 2 sessions per week, each interval of 2–3 days.

**Table 1 pone.0346717.t001:** Acupuncture treatment details based on the STRICTA 2010 checklist.

Item	Item number	Detail
1. Acupuncture rationale	(1a) Style of acupuncture	Traditional Chinese Medicine
	(1b) Reasoning for treatment provided, based on historical context, literature sources, and/or consensus methods, with references where appropriate	The treatment is carried out according to traditional acupuncture theory, previous studies, and the experts’ consensus.
	(1c) Extent to which treatment was varied	Standardised acupuncture treatment.
2. Details of needling	(2a) Number of needle insertions per subject per session	8
	(2b) Names of points used	Bilateral Taixi (KI 3), bilateral Dazhong(KI 4), bilateral Sanyinjiao (SP 6), Shenting (GV 24), and Baihui (GV 20).
	(2c) Depth of insertion, based on a specified unit of measurement, or on a particular tissue level	From 0.3–1 cun.
	(2d) Response sought	*Deqi* (numbness, soreness, heaviness, distention, etc.)
	(2e) Needle stimulation	Manual acupuncture
	(2f) Needle retention time	30 min
	(2g) Needle type	Sterile, disposable acupuncture needles (length, 25 mm; diameter, 0.25 mm; Hwato, China).
3. Treatment regimen	(3a) Number of treatment sessions	24
	(3b) Frequency and duration of treatment sessions	Twice per week (once per 2–3 days interval), for 12 continuous weeks.
4. Other components of treatment	(4a) Details of other interventions administered to the acupuncture group	/
	(4b) Setting and context of treatment, including instructions to practitioners, and information and explanations to patients	The trial will be implemented at departments in the outpatient clinics of nine hospitals (the West China Hospital, the Fourth People’s Hospital of Chengdu, the Sichuan Province People’s Hospital, Traditional Chinese Medicine Hospital of Pidu district, the Nanchong Second People’s Hospital, Meishan Hospital of traditional Chinese Medicine, Chengdu First People’s Hospital, the Rehabilitation Hospital of Sichuan Province and Hospital of Chengdu University of Traditional Chinese Medicine). All information and explanations will be provided to participants.
5. Practitioner background	(5) Description of participating acupuncturists	Trained, licensed acupuncturists with at least 6 years in acupuncture clinical practice.
6. Control or comparator interventions	(6a) Rationale for the control or comparator in the context of the research question, with sources that justify this choice	The treatment is carried out according to previous studies, and the experts’ consensus.
	(6b) Precise description of the control or comparator. If sham acupuncture or any other type of acupuncture-like control is used, provide details as for Items 1–3 above.	Sham acupuncture will be performed at 8 non-acupoints.
	(6b-1) Style of acupuncture	The sham acupuncture is invasive (penetrating the skin).
	(6b-2) Reasoning for treatment provided, based on historical context, literature sources, and/or consensus methods, with references where appropriate	The protocol for choosing the non-acupoints was developed in our previous clinical trial.
	(6b-3) Extent to which treatment was varied	Standardised sham acupuncture treatment.

**Table 2 pone.0346717.t002:** Details of the intervention in the acupuncture group.

Acupoint	Location	Manipulation
Taixi (KI 3)	Posterior to the medial malleolus, in the depression between tip of the medial malleolus and tendo calcaneus.	Subcutaneous insertion to a depth of 0.5–1 cun with manipulation for the *deqi.*
Dazhong (KI 4)	Under the medial malleolus of the foot, the medial anterior depression of the achilles tendon attachment.	Subcutaneous insertion to a depth of 0.3–0.5 cun with manipulation for the *deqi.*
Sanyinjiao (SP 6)	On the inside of the calf, 3 cun above the tip of the medial malleolus, posterior border of the medial border of the tibia.	Subcutaneous insertion to a depth of 0.5–1 cun with manipulation for the *deqi.*
Shenting (GV 24)	0.5 cun directly above the midpoint of the anterior hairline.	Subcutaneous insertion to a depth of 0.3–0.5 cun with manipulation for the *deqi*.
Baihui (GV 20)	5 cun directly above the midpoint of the anterior hairline, at the midpoint of the line connecting the apexes of the two auricles.	Subcutaneous insertion to a depth of 0.5–1 cun with manipulation for the *deqi.*

Note: 1 cun (≈25 mm) is defined as the width of the interphalangeal joint of the patient’s thumb.

#### Sham acupuncture group.

The sham acupuncture intervention will adhere to the Acupuncture Controls guideline for Reporting human Trials and Experiments (ACURATE) [32,33] (**Table 3**). It will involve shallow acupuncture 0.3–0.5 cun, inserted perpendicularly) at eight non-acupoints. The non-acupoint selection protocol was developed in our previous clinical trial [34] (**Table 4 and Fig 4**). Skin disinfection will precede needle insertion. However, there will be no stimulation, manipulation, or attempts to elicit the *deqi* sensation. Licensed acupuncturists will use single-use sterile needles (Hwato, Suzhou, China; 0.25 × 13 mm) for all procedures. Treatment sessions will last 30 minutes and continue for 12 weeks, 2 sessions per week, each interval of 2–3 days.

**Table 3 pone.0346717.t003:** Sham acupuncture intervention details based on the ACURATE checklist.

Category	Item	Description	Detail
1. Type of sham acupuncture	1a	Report the type of sham acupuncture.	Sham acupuncture will be performed at four non-acupoints (Shallow acupuncture, 0.3–0.5 cun.)
	1b	Report whether the sham acupuncture is penetrating or non-penetrating.	Penetrating
	1c	Rationale for using the chosen sham acupuncture.	Based on our previous clinical trial [34].
2. Details of sham acupuncture manipulation	2a	Report the number of sham acupuncture applied per subject per session.	8
	2b	Report the depth of sham acupuncture insertion (if there was no penetration, state this within the paper).	0.3-0.5 cun.
	2c	Report whether any response was observed during sham acupuncture manipulation (e.g., de qi or muscle twitch response).	Without attempting to yield the *deqi* sensation.
	2d	Report if there was any stimulation using sham acupuncture.	Without stimulation or manipulation.
	2e	Report if there was sham acupuncture retention.	30 min sessions.
	2f	Report details of other interventions administered in addition to sham acupuncture during one session.	Patients will be allowed to perform basic treatments such as blood pressure control, blood sugar control, and other supportive treatments.
3. Location of sham acupuncture	3a	Report the location of sham acupuncture (e.g., acupoint/non-acupoint or the exact location of the sites).	8 non-acupoints (Table 4 and Fig 4).
	3b	Explicitly state in the paper if the points are unilateral or bilateral.	8 non-acupoints on the left and right sides.
	3c	Describe the reason for the chosen location of sham acupuncture.	Based on our previous clinical trial.
4. Treatment regimen	4a	Report the number of treatment sessions.	30 min sessions over 12 weeks.
	4b	Report whether the number of sessions were identical between real and sham acupuncture treatments.	Both groups will be administered with the same, number of sessions, frequency and treatment duration.
	4c	Report the frequency and duration of treatment sessions.	30 min sessions over 12 weeks.
	4d	Report the total trial period.	12 weeks.
5. Practitioner	5a	Report whether the same practitioner is administering both real and control treatments (interventions).	All interventions will be performed by doctors of Traditional Chinese Medicine with more than 6 years of experience. They will administer both real and sham acupuncture.
	5b	Report whether there were conversations between practitioner and patient directly linked to the trial design, other than scripted instructions and preset information, prior to and during the treatment.	Throughout the course of treatment, acupuncturists will be asked to avoid discussing treatment options with patients.
6. Protocol and settings	6a	Report the information regarding sham acupuncture provided to participants.	Before randomization all participants will be informed that they will be allocated to the acupuncture group or sham acupuncture group.
	6b	Report whether the information given to patients include the term to openly state that the control is inert (e.g., “fake”, “sham”, “dummy”,”placebo”,...).	The participants will be informed that they will receive one of the two acupuncture treatments.
	6c	Describe how sham device was blinded from patients, and if done, how the blinding was assessed.	Patients will be treated separately to ensure blind evaluation.
	6d	If done, report any modification in the sham acupuncture treatment procedure, and reason for the modification.	Not Applicable.
	6e	Report any difference in the treatment settings between real and sham acupuncture.	The choice of acupoints and the depth of insertion varied.

Note: 1 cun (≈25 mm) is defined as the width of the interphalangeal joint of the patient’s thumb.

**Table 4 pone.0346717.t004:** Details of the intervention in the sham acupuncture group.

Non-acupoint	Location	Manipulation
Non-acupoint 1	At the medial arm on the anterior border of the insertion of the deltoid muscle at the junction of deltoid and biceps muscles. (On the right arm)	Punctured perpendicularly 0.3-0.5 cun.
Non-acupoint 2	At the medial arm on the anterior border of the insertion of the deltoid muscle at the junction of deltoid and biceps muscles. (On the left arm)	
Non-acupoint 3	Half way between the tip of the elbow and axillae. (On the right arm)	
Non-acupoint 4	Half way between the tip of the elbow and axillae. (On the left arm)	
Non-acupoint 5	Ulnar side, half way between the epicodylus medialis of the humerus and ulnar side of the wrist. (On the right arm)	
Non-acupoint 6	Ulnar side, half way between the epicodylus medialis of the humerus and ulnar side of the wrist. (On the left arm)	
Non-acupoint 7	Edge of the tibia 1–2 cm lateral to the Zusanli (ST36) horizontally. (On the right leg)	
Non-acupoint 8	Edge of the tibia 1–2 cm lateral to the Zusanli (ST36) horizontally. (On the left leg)	

Note: 1 cun (≈25 mm) is defined as the width of the interphalangeal joint of the patient’s thumb.

**Fig 4 pone.0346717.g004:**
[figure not shown]
The non-acupoints of sham acupuncture group.

#### Basic interventions.

During the clinical trial, patients will be allowed to continue receiving basic treatments, such as those for blood pressure control, blood sugar control, or other supportive medications. The details of these treatments, including the time of administration, dosage, frequency, and any reactions experienced by the patient, will be meticulously recorded.

### Outcomes

#### Primary outcome measures.

Cognitive function will be measured using the ADAS-Cog scale [35]. The primary outcomes will be the changes in the ADAS-Cog score from baseline to week 12 and from baseline to week 60. The ADAS-Cog, comprised of 12 tasks, evaluates various aspects of cognition, including memory, language, praxis (ability to perform actions), orientation, and attention. It is a widely used instrument in dementia research, with lower scores indicating less cognitive impairment.

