**Methods:**

This is a multicenter, single-blinded, randomized controlled trial (RCT) with a long-term follow-up.166 patients diagnosed with aMCI will be randomly divided into acupuncture group (AG) and sham acupuncture group (SA). The intervention will last for 12 weeks (2 sessions per week), follow-up for 48 weeks, and the study will last a total of 60 weeks. The primary outcomes are the changes in the Alzheimer’s Disease Assessment Scale-Cognitive (ADAS-Cog) score from baseline to week 12 and from baseline to week 60. Generalized estimating equations (GEE) will be used to assess the impact of the acupuncture intervention on outcome variables over time at baseline and weeks 12, 24, 48, and 60.

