### Statistical analysis

The data will be processed and analyzed by an independent statistician using IBM SPSS 26.0. An Intention-to-Treat (ITT) analysis approach will be adopted. Sensitivity analysis will use the Per-protocol (PP) analysis method. A two-sided *P-value* < 0.05 will indicate statistical significance. Descriptive statistics for continuous variables will include means and standard deviations (for normally distributed data) or medians and interquartile ranges (otherwise). Categorical variables will be presented as frequencies and percentages. Generalized estimating equations (GEE) will be used to assess the impact of the acupuncture intervention on outcome variables over time at baseline and weeks 12, 24, 48, and 60, with baseline measurement, time, group, and the group-by-time interaction included as covariates, as these factors may influence the efficacy of the acupuncture intervention. Patterns of missingness will be examined, and multiple imputation will be used assuming missing at random, with sensitivity analyses conducted where appropriate.

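### Two unordered primary outcomes with no success rule: depending on the rule, either the 5% trial-level error or the 90% power is lost

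*Protocol article*

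**What the plan says.** The Primary outcome measures section states: "The primary outcomes will be the changes in the ADAS-Cog score from baseline to week 12 and from baseline to week 60". The Methods part of the abstract says the same, and neither place ranks the two.

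The Statistical analysis section gives one general criterion: "A two-sided *P-value* < 0.05 will indicate statistical significance". It describes a GEE over the visits with a group-by-time interaction. It names no week-12 or week-60 contrast as primary, no order of testing and no division of alpha.

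The Sample size section gives one assumed effect, with no time point attached: "we anticipate an average effect of 3.5 in the acupuncture group and 1.5 in the control group, with a standard deviation of 3.5 between the" […]. From this, "we calculated a required sample size of 132 subjects (α = 0.05, 1 − β = 0.90, two-sided"). It then allows for dropout: "To account for a potential 20% loss to follow-up, we plan to enroll 83 patients in each group, for a total of 166 aMCI patients".

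Under Secondary outcome measures, item (1) lists the total ADAS-Cog again at weeks 12, 24, 36, 48 and 60, so both primary time points also appear as secondary.

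**The concern.** With two primary outcomes, the trial's conclusion depends on a rule for combining them, and the article gives none. The natural candidates lead to different designs. Counting a success at either time point allows two chances at 0.05. Requiring both means passing two hurdles, each with about a 10% chance of failure under the assumed effect. The sample size calculation covers neither case.

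Without a declared rule, the time point that carries the claim could be chosen after the results are known. That bears directly on the main question of whether acupuncture beats sham, at the end of treatment or in the long term.

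**Working it through.** **Inputs from the article.** Difference 3.5 − 1.5 = 2.0; SD 3.5; two-sided alpha 0.05; power 0.90; 1:1 allocation; 20% loss; two primary outcomes.

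**Assumptions (not in the article).** The correlation ρ between the week-12 and week-60 test statistics runs from 0 to 0.9. The same 2.0 difference and SD of 3.5 apply at both visits. There are 66 evaluable patients per arm at both visits.

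**1. Reproducing the stated size.** The normal formula is n = 2[(1.960 + 1.282) × 3.5 / 2.0]² = 64.4, so 65 per arm. The exact two-sample t-test needs 66 per arm, which is 132 in total, as stated. Dropout: 66 / 0.80 = 82.5, so 83 per arm and 166 in total, as stated. Power at 66 per arm is 90.3% (t) or 90.7% (normal). The stated figures are therefore those of one comparison at the full alpha.

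**2. Expected test statistic.** The standard error is 3.5 × √(2/66) = 0.609, so the expected z is 2.0 / 0.609 = 3.28 at each visit.

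**3. Two tests at 0.05, bivariate normal.** Under independence, the false-positive rate for either is 1 − 0.95² = 0.0975, and the power for both is 0.907² = 0.823. Over the range:

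| ρ | At least one false positive | Power, at least one | Power, both |
|---|---|---|---|
| 0 | 9.75% | 99.1% | 82.3% |
| 0.3 | 9.5% | 98.1% | 83.3% |
| 0.5 | 9.1% | 97.1% | 84.3% |
| 0.7 | 8.4% | 95.7% | 85.7% |
| 0.9 | 7.0% | 93.7% | 87.8% |

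These are normal approximations. On the t scale, joint power is slightly lower, about 81.5% (0.903²) to 87%. If both are required, a false claim needs a false positive on at least one true null, so the error cannot exceed 5%.

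**4. Splitting alpha.** At 0.025 each, the critical value is 2.241 and power per outcome is Φ(3.283 − 2.241) = 85.1% (normal) or 84.4% (t). Restoring 90% per outcome needs 78 per arm by t-test. With dropout this is 78 / 0.80 = 97.5, so 98 per arm and 196 in total against 166.

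**5. Both required at 90% joint power.** This needs 71 (ρ = 0.9) to 80 (ρ = 0) evaluable per arm, that is 71 / 0.80 = 88.75, so 89, to 80 / 0.80 = 100 enrolled per arm.

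**6. If the effect fades.** Should the week-60 difference be 1.5 or 1.0 instead of 2.0 (an assumption for illustration), power for that test alone at 66 per arm is 69% or 37% (normal). The joint powers above are then too high.

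**The case against.** *Both stated properties fail.* A reader might infer that the 5% error and the 90% power are lost together. They are not. An either-suffices rule raises the error but leaves power above 90%. A both-required rule lowers power but holds the error. For each comparison taken alone, the stated 5% and 90% are correct.

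*The plan permits a claim on whichever time point succeeds.* The article does not say this. It describes one GEE and a general threshold, claims no family-wise rate and states no either-suffices rule. The defect is that the rule is open.

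*The error is nearly doubled.* That fits only low to moderate correlation. The two changes share patients, scale and baseline, so independence is an upper bound, and at ρ = 0.9 the figure is 7.0%.

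*Two objectives, two questions.* The Objective section separates efficacy and safety against sham from the long-term effect. If week 12 answered the first and week 60 the second, with separate claims, the need to adjust would be debatable. This softens the point but does not settle it, because the section ties neither objective to a week.

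*The rule may be in the SAP.* An ordering could be there, and the absence of a rule can be asserted only of this article. But no rule that splits alpha or requires both would deliver the stated 90% at 132 evaluable patients under the stated effect. Only an ordered test keeps that figure, and then for the first test alone.

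*Attrition may be later.* If 75 per arm remained at week 12 and 66 at week 60 (an assumption), joint power would be about 84% to 89%, still below 90%.

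*The secondary listing.* Repeating weeks 12 and 60 there is redundant; it does not change the error rate.

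**Conclusion.** The point holds in this form: two unordered primary outcomes, one 0.05 threshold and a single-comparison sample size leave the trial's success criterion undefined, and each simple way of combining the two tests gives up one stated property. The cost is a trial-level error of about 7.0% to 9.75% if either suffices, joint power of about 82% to 88% if both are required, or about 84% power per outcome under a Bonferroni split.

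These sizes rest on an assumed correlation of 0 to 0.9. The power figures also assume the full 2-point difference and 66 evaluable patients per arm at both visits. The direction of the conclusion does not change anywhere in that range. Because it governs the main claim, the rule should be settled before unblinding.

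**What to change.** Before unblinding, state a fixed sequence in the protocol, SAP and registry entry, with both tests taken as named contrasts from the GEE. One form is:

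- Test the week-12 group contrast at two-sided 0.05.
- Test the week-60 group contrast at two-sided 0.05 only if week 12 is significant; otherwise report week 60 descriptively.

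If the long-term effect is the main question, the sponsor may put week 60 first; either order controls the error if declared in advance.

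Two further edits belong with this. In the Sample size section, say which time point the assumed 2-point difference refers to, and restate the 90% power as that of the first test only, with lower power for success at both. That 90% holds only if the assumed difference applies at the time point placed first. In the Secondary outcome measures section, remove weeks 12 and 60 from the total ADAS-Cog item, leaving weeks 24, 36 and 48.

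The cost is a few sentences and no extra patients: 166 remains the target and the family-wise error is 5%. The downside is that the second time point cannot be claimed if the first fails.
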